### Participants

Patients are identified and assessed for eligibility based on several criteria. Inclusion criteria are patients aged >18 years who provide informed consent to be part of the study. Exclusion criteria are patients aged <18 years and those who are unable to provide informed consent, have an allergy to the electrocardiogram or sensor electrodes or skin conditions at the sensor site, have an implantable electronic cardiac device (which responds to minute ventilation and can interfere with respiratory rate measurement technology), or are already taking part in another study.

Nursing staff, including both registered nurses and health care assistants, are invited to participate in the study. After recruiting 100 patients, all staff on the delegation log will be invited to complete a structured questionnaire, and a subset who volunteer will be selected for a follow-up interview at the end of the study period.

### Ethical Considerations

All participants will be required to provide informed consent. Ethics approval was granted by the Health Research Authority and Health and Care Research Wales (approval reference 24/YH/0073; Integrated Research Application System project ID 335808) on April 18, 2024. This study is conducted in accordance with the principles of good clinical practice, the UK policy framework for health and social care research, and the Declaration of Helsinki. All patient data will be anonymized, and patients will be assigned a unique study ID. No identifiable patient data will be shared with a third party.

### Trial Registration

The trial is registered with the International Standard Registered Clinical/Social Study Number (ISRCTN15518094).

### Outcomes

Despite the growing interest in continuous vital sign monitoring, most prospective trials are limited by assessing only feasibility and acceptability and are not always powered for patient-centered outcomes [20,22-29]. There is still a clear lack of understanding of how continuous physiological data translate into alerts, how these alerts influence clinician assessment and intervention, and whether these actions ultimately improve patient outcomes. The WARD-AMS study design assesses the full monitoring-alert-action-outcome pathway.

### Primary End Point

The primary end point is the time (in minutes) from the first device-defined deterioration episode (T_0_) to the first objective escalation event (T_action) among patients who experience at least one device-defined deterioration episode during the monitoring period.

#### Definition of T_0_ (Time Zero)

T_0_ is defined as the time stamp of the first device-defined deterioration episode for each patient according to the prespecified WARD-AMS deterioration criteria: pulse rate of <45 bpm or >130 bpm sustained for ≥30 seconds, respiratory rate of <4 breaths per minute sustained for ≥30 seconds or >30 breaths per minute sustained for ≥120 seconds and apnea sustained for ≥30 seconds, and peripheral oxygen saturation of <85% sustained for ≥90 seconds or <80% without delay.

#### Definition of T_Action (Escalation Event)

T_action is defined as the earliest time stamp after T_0_ at which any of the following prespecified escalation events occurs:

Activation of an RRT call: time of official call log in the switchboard or outreach databaseUnplanned transfer to higher level of care: time of actual bed movement from the ward to the ICU, high-dependency unit (HDU), or critical care unit as recorded on the EPRNew high-acuity treatment orders (time stamp of order entry on the EPR): new intravenous (IV) fluid; new start of vasopressor or inotrope; new start of high-flow oxygen, continuous positive airway pressure, or noninvasive ventilation; and new start of broad-spectrum IV antibioticsTime stamp of alarm acknowledgment on the nursing log

For each patient with at least one eligible deterioration episode, only the first deterioration episode (first T_0_) will be included in the primary analysis. T_action is the earliest qualifying escalation event occurring after that T_0_. If at least one escalation event occurs after T_0_, the primary outcome is calculated as follows and expressed in minutes:

$$\text{Primary outcome}=T_{\text{action}}-T_{0}$$

If no escalation event occurs before censoring, the observation is right censored at the prespecified censor time (eg, end of monitoring period, discharge, death, or withdrawal from the study).

Acknowledgment of clinical deterioration can occur through several legitimate pathways in routine ward practice; therefore, relying on a single indicator may risk meaningful clinical response detection. To address this, a composite definition of T_action is chosen to ensure that the earliest objective, time-stamped event is captured. The same criteria are applied across both trial arms.

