## Methods

### Study Design

A prospective, interventional randomized controlled trial will be conducted using a mixed methods approach. It is an open-label, 2-arm study that aims to recruit 200 patients over a 1-year period. Patients will be randomized using an online tool (Greenlight Guru Clinical) on a 1:1 basis into an alerting and nonalerting group ( Figure S1 in Multimedia Appendix 1). This study will be conducted on 2 postsurgical wards at the West Middlesex University Hospital, London, with a capacity of 64 beds, providing orthopedic, general surgical, urological, gastroenterological, and gynecological care.

Patients are screened after the morning ward round, and those who are expected to remain in hospital for at least 1 night are approached by the research team for consent and assessment against the inclusion and exclusion criteria. Most of these patients are postoperative, although a small number are preoperative. All patients will be fitted with a continuous vital sign monitor (Portrait Mobile; GE HealthCare) from recruitment until either discharge from hospital or transfer to another unit. This CE-marked device (European Union certificate CR-03-1004-804-22) consists of 2 wearable sensors: a wrist-mounted saturation probe measuring both the oxygen saturation and pulse rate and a chest sensor measuring the respiratory rate. Both groups will have vital signs monitored as per the standard of care, intermittently acquired every 4 to 6 hours by health care staff using the National Early Warning Score 2 for identification and escalation of a deteriorating patient [19].

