Only the alerting group will have their continuous vital signs transmitted to a visible central viewer dashboard located at the nursing station and have audible alarms enabled on both the bedside hub monitor and the central viewer. All ward health care staff have access to real-time patient data and alarms; however, the nurse in charge is responsible for recognizing alarms, logging them, and informing the bedside nurse to respond appropriately. The intervention in this trial is the activation of real-time alerting through the continuous vital sign monitor, and alarms are managed entirely by the usual ward clinical team. They follow standard hospital escalation protocols, escalating deteriorating patients to the ward physician during daytime hours, the on-call physician out of hours, or the critical care outreach team. The critical care outreach team (also known as the rapid response team [RRT]) is an existing hospital team of specialized nurses who respond to acutely unwell patients requiring urgent assessment or intervention outside of the ICU. In the nonalerting group, health care staff are blinded to the continuous monitoring data.

To address alarm fatigue, several considerations have been taken. The alerting thresholds and announcement delays were derived from the Continuous Vital Sign Monitoring in Surgical Wards (COSMOS) pilot study, which conducted its initial phase by analyzing alarm data (pulse rate of <45 beats per minute [bpm] or >130 bpm sustained for ≥30 seconds, respiratory rate of <4 breaths per minute sustained for ≥30 seconds or >30 breaths per minute sustained for ≥120 seconds, apnea sustained for ≥30 seconds, and peripheral oxygen saturation of <85% sustained for ≥90 seconds or <80% without delay) [20]. These clinically validated alarm thresholds and built-in delay minimize false alerts caused by artifacts or transiently deranged vital signs. The central viewer is stationed at the nursing bay, beside the desk of the nurse in charge, who triages alarms. In addition, all ward staff received structured device training from GE HealthCare representatives focusing on correct interpretation, prioritization, and escalation of alarms.

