### Exploratory End Point

Exploratory end points will further evaluate a broader range of clinical, operational, alarm-related, and user experience outcomes. Time-to-event clinical end points include time from T_0_ to initiation of key treatments, such as antibiotics, IV fluids, vasopressors, oxygen, or advanced respiratory support. Additional timing end points include the interval from T_0_ to RRT activation and from T_0_ to unplanned transfer to an HDU or ICU. Resource use outcomes will be explored, including length of hospital stay, rates of admission to higher-level care, frequency of RRT activation, and in-hospital mortality.

Analysis of alarms will include identifying the frequency, type, and clinical relevance of alerts triggered by the continuous vital sign monitor, as well as the proportion of alarms that are associated with escalation events. Patient and health care staff experience will be evaluated via structured questionnaires and semistructured interviews.

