### Data Governance and Management

The study data will be extracted by a staff member employed as a business intelligence research analyst at Chelsea and Westminster Hospital National Health Service Foundation Trust. These data are stored on secure trust servers, with access restricted to the core study team. These data will be retained for 15 years in accordance with trust policy. An audit trail is available in the EPR.

Each participant will be assigned a unique trial ID during randomization. Variables extracted will include demographics (eg, date of birth, sex, and ethnicity), medical and medication history, vital signs, blood tests, transfer of care, and length of stay. Missing data will not be imputed and will be analyzed as available.

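### T_action has no event for ward or on-call physician escalation or for ordinary oxygen, so control responses can be timed late or censored while alerting responses are timed from the alarm log

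*Protocol article*

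**What the plan says.** The Study Design section describes how ward staff escalate: "escalating deteriorating patients to the ward physician during daytime hours, the on-call physician out of hours, or the critical care outreach team". In both arms, routine observations are taken every 4 to 6 hours, "using the National Early Warning Score 2 for identification and escalation of a deteriorating patient". In the nonalerting arm "health care staff are blinded to the continuous monitoring data". In the alerting arm "the nurse in charge is responsible for recognizing alarms, logging them, and informing the bedside nurse to respond appropriately".

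The definition of T_action is a closed list of four kinds of event:

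- a logged rapid response (outreach) call;
- an unplanned move to the ICU, HDU or critical care;
- new high-acuity orders, namely "new intravenous (IV) fluid; new start of vasopressor or inotrope", "new start of high-flow oxygen, continuous positive airway pressure, or noninvasive ventilation" and broad-spectrum IV antibiotics;
- an alarm acknowledgment on the nursing log.

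A patient with no listed event is right censored. The section justifies the composite by saying that deterioration may be recognized by more than one proper route on an ordinary ward, and it says that both arms are held to the same list.

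The Exploratory End Point section times key treatments from T_0, "such as antibiotics, IV fluids, vasopressors, oxygen, or advanced respiratory support". Oxygen stands there as an item separate from advanced respiratory support.

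**The concern.** Two of the three named escalation routes have no T_action event of their own. Ordinary oxygen is also absent, although low saturation is one of the criteria that start the clock. The composite is thus narrower than its own rationale.

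The list is the same on paper but does not work the same way in the two arms. The only item that records acknowledgment is tied to a device alarm, and control staff neither see nor hear one. Take a patient whose low saturation is found at a routine round, who is given ordinary oxygen and is reviewed by the ward physician. In the control arm none of this stops the clock. In the alerting arm the clock will usually have stopped already, at the log entry.

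At stake is whether the primary hazard ratio measures faster response or partly measures which arm's responses can be recorded. About 30 patients are expected in the primary analysis, so a few control responses moved later or censored would matter.

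**Working it through.** **1. The plan's own figures.** 0.15 × 200 = 30 patients with an event, about 15 per arm. 154 / 60 = 2.57, which rounds to the stated hazard ratio of 2.6. Both reproduce.

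**2. The sections side by side.**

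| Response | Where the article names it | In T_action? |
|---|---|---|
| Outreach call | Study Design | Yes |
| Ward physician, daytime | Study Design | No event of its own |
| On-call physician, out of hours | Study Design | No event of its own |
| Ordinary oxygen | Exploratory End Point | No |
| High-flow oxygen, CPAP, NIV | T_action definition | Yes |
| New IV fluid, broad-spectrum IV antibiotics | T_action definition | Yes, including when a ward physician orders them |
| Alarm acknowledgment | T_action definition | Yes, but only the alerting arm has an alarm to acknowledge |

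**3. Size with no true effect.** Inputs from the article: mean response 154 minutes, here given to both arms, and 15 patients per arm. Assumptions: exponential times; every alerting response is logged; a share p of control responses falls on a listed event at the true response time; the log-rank test is two-sided at 5%. The article does not give p. Two assumptions cover the remaining 1 − p:

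- A: no listed event follows, and the patient is censored at 48 hours.
- B: a listed event follows after a further exponential delay with mean 240 minutes.

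| p | Not captured | Apparent HR, A | Log-rank rejects, A | Apparent HR, B |
|---|---|---|---|---|
| 0.8 | 20% | 1.8 | 30% | 1.3 |
| 0.6 | 40% | 3.1 | 74% | 1.6 |
| 0.4 | 60% | 5.7 | 97% | about 2.0 |

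A hand check of A: with rate λ = 1/154 per minute, the alerting hazard is λ and the control hazard is pλe^(−λt) / [(1 − p) + pe^(−λt)]. Their ratio is 1 + [(1 − p)/p]e^(λt).

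- At p = 0.8 it starts at 1 + 0.25 = 1.25 and is 1 + 0.25 × 2 = 1.5 at the median time of 154 × ln 2 = 107 minutes.
- At p = 0.6 it starts at 1 + 0.667 = 1.67 and is 1 + 0.667 × 2 = 2.33 at the median.

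It keeps rising after that, which agrees with fitted averages of 1.8 and 3.1.

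A variant of B with a fixed 240-minute delay and 24-hour follow-up rejects in 19% of trials at 25% not captured and in 46% at 50%.

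**4. The same loss in both arms.** This is the situation if alarm acknowledgment is removed and nothing is added. Under A with p equal in the two arms:

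- With no true effect, the hazard ratio is about 1.0 at p = 0.8, 0.6 and 0.4, and rejection stays near 5%.
- With true means of 60 and 154 minutes, rejection falls from 69% at p = 1 to about 17% at p = 0.8 and 9% at p = 0.6.

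So the inflation in step 3 needs both the omission and the alarm log. The omission alone dilutes the effect and costs power.

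**The case against.** The strongest defense is that the list was built from objective time stamps. Calls, bed moves and orders carry them; a conversation with a physician may not. This stands as a reason for caution about physician-contact times. It does not explain leaving out ordinary oxygen, since the plan already intends to time it from T_0 as an exploratory end point.

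Second, a reader might infer that a control patient who is properly managed is scored as never escalated. The documents do not support that. A ward physician's order for new IV fluid or broad-spectrum IV antibiotics counts, an outreach call counts, and the clock runs until the end of monitoring, discharge, death or withdrawal. Many control patients would get a late T_action rather than none.

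Third, a reader might infer that the target hazard ratio of 2.6 would be passed without benefit once 20% to 40% of control responses are unlisted. That holds only under assumption A. Under B it is not reached even at 60%. Nor does the article say that the omitted routes are the most usual control response; it gives no frequency by route.

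Fourth, it may be said that a repeat NEWS2 set should have been counted. The article names NEWS2 as a tool for identification and escalation, not as an escalation event. A score reaching a trigger is detection, whereas T_action is defined as acknowledgment or clinical action.

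Finally, recruitment has ended in an open-label trial, so replacing the primary list now is open to challenge. That stands, and it shapes the fix.

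**Conclusion.** The point holds in a limited form. The T_action list contradicts the article's own escalation pathway, its list of key treatments and the stated reason for the composite. Applied as written, it can understate control response and favor the alerting arm.

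The direction follows from the text, provided that alarm acknowledgment stays in the composite. The size does not. With no true effect and 20% to 40% of control responses not captured, the apparent hazard ratio lies between about 1.3 and 3.1, depending on whether those patients reach a listed event later or are censored. The share, the exponential times, the 240-minute mean delay, the 48-hour censoring and complete logging in the alerting arm are all assumptions.

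The inflated values belong jointly to this omission and to alarm acknowledgment, and should not be counted twice if that item is also criticized. Removing alarm acknowledgment alone would not be enough: it would exchange the bias for a loss of power in an analysis of about 30 patients.

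**What to change.** Reconcile the escalation routes in Study Design, the T_action list and the key treatments in Exploratory End Point. This concerns only what is counted, not how patients are managed.

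Before any arm-level results are seen, prespecify and document an analysis of the primary end point in which T_action also counts, identically in both arms:

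- the EPR time of a new oxygen order or start of any type;
- where the EPR time-stamps it, escalation to or review by the ward or on-call physician.

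Report it beside the current list, and limit the conclusion if the two differ. Do not count a NEWS2 set alone as escalation in the main definition; at most, show it as a further sensitivity analysis.

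Timing matters. The abstract says that analysis is ongoing, while the Results section places cleaning after data collection ends, projected for February 2026. The record should state what had been seen when the analysis was added.

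The cost is a slightly larger EPR extract. The variables named for extraction include "medical and medication history, vital signs, blood tests, transfer of care, and length of stay", but not physician contact, and those times are likely to be less precise than order times.

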### Statistical Analysis

#### Primary End Point Analysis

Among the 2 groups (blinded and unblinded), the primary comparison will be the time from device-defined deterioration to objective escalation. The primary analysis will be performed in the population of patients who experience at least one device-defined deterioration episode, restricted to only 1 episode per patient (the first). Time-to-event methods will be used, with Kaplan-Meier curves constructed for each arm to visualize the distribution of time to escalation. The primary hypothesis test will use a log-rank test comparing the survival curves between arms, and a Cox proportional hazard model will be fitted with the interventional arm as the main exposure to estimate the hazard ratio for escalation (intervention vs control) with corresponding 95% CIs. The Cox model will be adjusted for key baseline covariates (age, sex, and comorbidity burden [Charlson Comorbidity Index]).

Patients with a device-identified deterioration without an escalation event during follow-up until their censor time will be treated as right censored in all time-to-event analyses. Proportional hazard assumptions will be evaluated using standard diagnostics such as Schoenfeld residuals. If these assumptions are materially violated, alternative or supplementary summaries such as restricted mean time to escalation up to a predefined time horizon may be reported in sensitivity analyses.

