#### Exploratory Analysis

Analysis of all clinical end points involving time-to-event data will be conducted using survival analysis methods, specifically Kaplan-Meier curves and log-rank tests to assess differences between the alerting and nonalerting arms.

Length of hospital stay will undergo additional analysis using nonparametric tests to evaluate differences in median length of stay between the 2 study arms. Secondary outcomes presented as categorical variables, such as frequency of HDU or ICU admission and RRT activation, will be compared using chi-square tests. These will be conducted using RStudio (Posit PBC) [33].

Quantitative data from both the health care staff and patient questionnaires will be analyzed to illustrate frequency distributions and central tendencies regarding system usability, satisfaction, and other outcome measures. Likert-scale responses will be numerically scored and statistically analyzed using RStudio [33].

Interview transcripts will be analyzed by generating a set of codes that will be predefined from existing literature and serve as initial labels to index relevant data segments. This will be refined through iterative coding and thematic consolidation to ensure accurate and meaningful categorization by merging similar codes and splitting overly broad codes. To enhance validity, this method will be performed by 2 independent researchers until thematic consensus and data saturation are reached.

The quantitative outcomes (time to acknowledgment of deterioration, time to treatment initiation, escalation of care, and alarm analyses) will be compared with qualitative themes from the staff and patient questionnaires and interviews using a triangulation approach for a better understanding of the effect and implementation of continuous vital sign monitoring. A joint display table will be developed aligning key quantitative results with corresponding qualitative findings, identifying areas of convergence, complementarity, or divergence.

This integrated mixed methods approach aims to facilitate a comprehensive understanding of the usability, acceptability, and practical implications of the Portrait Mobile system.

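### The primary end point has no fixed response window and no link to the episode, so late unrelated orders count as responses; separately, censoring discharge and death makes the Kaplan-Meier curves overstate escalation

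*Protocol article*

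**What the plan says.** All references are to the protocol article.

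- **Response.** Under Definition of T_Action, "T_action is the earliest qualifying escalation event occurring after that T_0". No maximum interval is given. The qualifying treatment orders include "new intravenous (IV) fluid; new start of vasopressor or inotrope", and also new broad-spectrum IV antibiotics. Nothing requires the order to relate to the T_0 episode. An alarm acknowledgment on the nursing log qualifies too.
- **No response.** If no qualifying event occurs, "the observation is right censored at the prespecified censor time (eg, end of monitoring period, discharge, death, or withdrawal from the study". Under Primary End Point Analysis such patients "will be treated as right censored in all time-to-event analyses".
- **Length of follow-up.** Under Study Design the monitor is worn "from recruitment until either discharge from hospital or transfer to another unit", so the outer limit differs from patient to patient and can be days after T_0.
- **Analysis.** The primary test is the log-rank test and the effect measure is the Cox hazard ratio, with "Kaplan-Meier curves constructed for each arm to visualize the distribution of time to escalation". For the exploratory end points, "Analysis of all clinical end points involving time-to-event data will be conducted using survival analysis methods, specifically Kaplan-Meier curves and log-rank tests".
- **Time horizon.** One is mentioned only as a fallback if proportional hazards fails: "restricted mean time to escalation up to a predefined time horizon may be reported in sensitivity analyses". No value is given.
- **Blinding.** Under Study Design, staff caring for the nonalerting group do not see the continuous data.

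**The concern.** There are two separate problems, and the first is the weightier.

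**Open window.** The end point is meant to measure how quickly staff respond to a particular episode. On a surgical ward that also takes some preoperative patients, a new fluid or antibiotic order can arise for reasons unconnected with an alarm days earlier. Under the stated rule it is still the response to that alarm. The effect is unlikely to be equal in the two arms. A patient who is answered quickly has no time left to collect an unrelated order, and alarm acknowledgment, the quickest route, is practically closed to controls. Unrelated orders therefore accumulate mainly among controls who had no true response, and they are analysed as slow responses. This reaches the primary estimate itself.

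**Discharge and death as censoring.** A patient who is discharged or dies can no longer be escalated on the ward. Kaplan-Meier redistributes that patient's probability to those still at risk, so 1 minus Kaplan-Meier exceeds the proportion actually escalated. The curves are nevertheless offered as the distribution of time to escalation. The exploratory intervals from T_0 to rapid response call, treatment and HDU/ICU transfer are handled in the same way.

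**Working it through.** **1. The plan's own figures (Sample Size).** Under exponential times, 154/60 = 2.57, which rounds to the stated 2.6. Patients with an alarm: 200 × 0.15 = 30. Both reproduce.

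**2. Unrelated orders.** The document gives no discharge times, no share of true responders and no rate of unrelated orders. Assumed: 50% of control and 80% of alerting patients truly respond, at means of 154 and 60 min (the plan's figures); discharge at a mean of 48 h; unrelated qualifying orders at a mean of 24, 48 or 96 h; all times exponential.

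Let r, u and d be the rates of true response, unrelated order and discharge. For a responder, P(unrelated order comes first) = u/(r+u+d) and P(any event) = (r+u)/(r+u+d). For a non-responder both are u/(u+d). For a window W, multiply each by 1 − exp(−total rate × W).

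Worked case, control, unrelated orders at 48 h: r = 1/154 = 0.006494 and u = d = 1/2880 = 0.000347 per min, total 0.007188.
- Open-ended: responders 0.0483 unrelated and 0.9517 any event; non-responders 0.5 for both. Mixed 50:50, 0.274 unrelated out of 0.726 events = 38%.
- Within 6 h: the factors are 1 − exp(−2.588) = 0.925 for responders and 1 − exp(−0.25) = 0.221 for non-responders. Unrelated 0.078 out of 0.495 events = 16%.
- Alerting arm, open-ended: 0.8 × 0.020 + 0.2 × 0.5 = 0.116 unrelated per patient. So 0.274/(0.274 + 0.116) = 70% of the unrelated orders fall in the control arm.

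Hazard ratios come from simulation of the same model.

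| Mean time to unrelated order | Unrelated share of control events, open-ended | Same, 6 h | HR, open-ended | HR, 6 h |
|---|---|---|---|---|
| 24 h | 47% | 27% | 2.1 | 2.6 |
| 48 h | 38% | 16% | 2.25 | 2.8 |
| 96 h | 28% | 9% | 2.4 | 2.9 |

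With no unrelated orders at all, the same model gives an HR of about 2.8 to 2.9 open-ended and about 3.0 within 6 h. A small part of the gap between the two HR columns is therefore due to non-proportional hazards. The larger part is contamination.

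**3. Kaplan-Meier against cumulative incidence.** With constant hazards, mean response m and mean discharge D, 1 minus Kaplan-Meier tends to 100%, while the true final proportion escalated is D/(D + m).

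| Assumed mean discharge | Control, m = 154 min | Alerting, m = 60 min |
|---|---|---|
| 24 h | 1440/1594 = 90.3% (excess 9.7 points) | 1440/1500 = 96.0% (4.0) |
| 48 h | 2880/3034 = 94.9% (5.1) | 2880/2940 = 98.0% (2.0) |
| 72 h | 4320/4474 = 96.6% (3.4) | 4320/4380 = 98.6% (1.4) |

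The excess grows when qualifying events arrive slowly relative to discharge. In the 48 h case of step 2, the control curve at 72 h reads 88.9% against a true 71.5%, an excess of 17.4 points. Non-response alone does not do this: with 50% responders and no unrelated orders the figures are 49.9% and 47.4%. For a slow exploratory event, assumed at a mean of 96 h, 1 minus Kaplan-Meier at 72 h is 52.8% against a true 19.5%, 29.8% or 35.4% for mean discharge at 24, 48 or 72 h.

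**4. Events kept by a 6 h window** (planning figures, every patient a responder, discharge at a mean of 48 h). Within 6 h, 86.8% of control and 97.7% of alerting patients have an event: 15 × 0.868 + 15 × 0.977 = 27.7 of 30. Open-ended: 15 × 0.949 + 15 × 0.980 = 28.9.

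**The case against.** The best defence is that the primary inference does not rest on the curves. With discharge and death censored, the log-rank test and Cox model compare cause-specific hazards, a legitimate answer to whether alerting speeds response. Kaplan-Meier is there for display. This stands: a reader might infer that the primary test is invalid because of competing events, and the document does not support that.

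A reader might also infer overstatements of 20 to 30 points in the primary curves. That needs a mean response near 48 h, far from the planned 154 and 60 min, at which the excess is single-digit. Nor is follow-up literally unlimited: it ends at end of monitoring, discharge, death or withdrawal. What is missing is a fixed response window. And it is tempting to add that censoring when the device comes off discards usable record data. Because the device is worn until discharge or transfer, and the Results section says that all 200 patients completed monitoring, there is little to support this.

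Finally, the list of censoring times is introduced as examples, and the detail may sit in an analysis plan that is not shown. That would excuse silence. It does not excuse the rules that are stated: the first qualifying event at any time after T_0 counts, discharge and death are right censored in all time-to-event analyses, and Kaplan-Meier displays the distribution. The rates used for unrelated orders and discharge remain assumptions.

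**Conclusion.** The point holds in two parts of unequal weight. The absence of a response window and of any link to the episode lets unrelated orders count as responses, mostly in the control arm, and would tend to pull the hazard ratio towards 1. On the assumptions shown, 28% to 47% of control events would be unrelated, and the hazard ratio would be about 2.1 to 2.4 instead of 2.6 to 2.9 within 6 h. If nearly every control responded at the planned speed, the effect would be small.

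The Kaplan-Meier overstatement is a matter of how the curves are read. It is modest at the planning figures, and larger where qualifying events come slowly relative to discharge, as may be so for the exploratory end points. It does not undermine the log-rank test or the cause-specific hazard ratio.

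**What to change.** - Fix a response window from T_0 for the primary analysis, for example 6 h, the upper end of the plan's own 4-to-6-hourly observation interval. Report 24 h and the open-ended version as sensitivity analyses.
- Fix and date this before arm-level results are seen. The Abstract says that analysis is ongoing, while the Results section places cleaning and preparation after February 2026. If results have already been seen, report the windowed analysis as a labelled sensitivity analysis.
- Keep the log-rank test and Cox model, and describe both as cause-specific.
- Replace or accompany the Kaplan-Meier curves with Aalen-Johansen cumulative incidence, treating discharge and death without escalation as competing events, for the primary and all exploratory T_0-based end points.

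The cost is some wording and standard code. The downside is that genuine escalations after the window leave the primary analysis. At the planning figures about 2 of 30 patients have no event within 6 h: about one is a late escalation (28.9 − 27.7 = 1.2), and about one is discharged first and has no event in the open-ended version either (30 − 28.9 = 1.1).
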